**Fig. 1 Fig1:**
[figure not shown]
The Consolidated Standards of Reporting Trials (CONSORT) diagram of the study

**Fig. 2 Fig2:**
[figure not shown]
The experimental flowchart for the clinical trials

The primary outcomes of the study are the SCs-specific markers measured in muscle (Pax7^+^, MyoD^+^ cells per type I/II myofibers), the macrophages’ markers measured in muscle (cluster of differentiation 11b marker (CD11b^+^), cluster of differentiation 206 marker (CD206^+^) cells per myofiber), the myogenesis-related markers measured in muscle (Myf5, MyoD, myogenin, MRF4 and myostatin mRNA expression levels), the cell signaling markers measured in muscle (GPX-3, SOD-2, Trx-1, insulin-like growth factor 1 (IGF-1), Notch1, Wnt3 protein expression levels), and the oxidative stress markers measured in muscle (GSH, oxidized glutathione (GSSG), protein carbonyls (PC) and malondialdehyde (MDA)). The secondary outcomes are the oxidative stress markers measured in blood (total antioxidant capacity (TAC) in serum, GSH, GSSG, catalase (CAT) and hemoglobin (Hb) in red blood cell lysates), and the inflammatory markers measured in blood (C-reactive protein (CRP), tumor necrosis factor alpha (TNF-α), interleukin (IL)-6, IL-8, IL-10), blood creatine kinase activity (CK) as a marker of muscle damage and serum cortisol). Other outcomes include body mass, height, body mass index (BMI), total and regional fat mass, lean mass and body fat, RMR, number of steps/day and time spent at sedentary, light, moderate, vigorous and moderate-to-vigorous PA, total daily energy intake and expenditure, daily intake of carbohydrate, fat, protein, vitamin A, vitamin C, vitamin D, vitamin E, selenium, zinc and magnesium, VO_2max_, knee extensors’ (KE) maximal eccentric and concentric peak torque and DOMS.

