All analyses and reporting of the results will comply with the Standard Protocol Items: Recommendations for Interventional Trials (SPIRIT) Statement for reporting randomized clinical trials (RCTs) [57]. Results of participant’s baseline characteristics and outcome variables (primary, secondary and other) will be summarized using descriptive statistics and will be expressed as mean (standard deviation) or median (range) for continuous variables. Data normality will be examined using the Kolmogorov-Smirnov and the Shapiro-Wilk tests. If our data sets follow normal distribution, parametric tests will be applied. Baseline comparisons on the LR and HR groups (anthropometrics, body composition, strength, VO_2max_, dietary profile, PA) will be performed using a one-way ANOVA test. Time- and trial-effect comparisons within and between trial (NAC or placebo) in the LR and HR groups will be analyzed using a two-way repeated-measures ANOVA test with a Bonferroni correction for pairwise comparisons. If the data normality is violated, non-parametric tests will be applied. Baseline comparisons on the LR and HR groups will be performed using a Kruskal-Wallis test. Time-effect comparisons within trial (NAC or placebo) in the LR and HR groups will be analyzed using a Friedman test accompanied by Wilcoxon signed-rank test for pairwise comparisons. Trial-effect comparisons between trials (NAC vs placebo) in the LR and HR groups will be analyzed using a Kruskal-Wallis test accompanied by a Mann-Whitney *U* test for pairwise comparisons. Pearson’s correlation analysis will also be used to examine possible relations among variables. Correlation coefficients of r < 0.2, 0.2 < r < 0.7 and r > 0.7 will be defined as small, moderate and high, respectively. The level of statistical significance will be set at *p* < 0.05. Effect sizes (ES) and confidence intervals (95% CI) will be calculated on results of all dependent variables using the Hedge’s *g* method, corrected for bias. ES will be interpreted as none, small, medium-sized and large for values 0.00–0.19, 0.20–0.49, 0.50–0.79 and ≥ 0.8, respectively. Multiple-imputation analysis will also be utilized to handle missing data during data collection and sensitivity analyses will be executed to evaluate the robustness of the results [58]. Statistical analyses will be performed using the SPSS 20.0 software (IBM Corp., Armonk, NY, USA).

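### Twenty-one muscle markers are co-equal primary outcomes tested at 0.05 with no correction across markers, so 0.05 is not the error rate of the primary objective

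*Protocol article*

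**What the plan says.** The paragraph after Fig. 2, in the part of the article on study overview and design, begins "The primary outcomes of the study are the SCs-specific markers measured in muscle" and names five families:

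- satellite-cell markers: "Pax7^+^, MyoD^+^ cells per type I/II myofibers"
- macrophage markers: CD11b+ cells and "cluster of differentiation 206 marker (CD206^+^) cells per myofiber"
- myogenesis markers: "Myf5, MyoD, myogenin, MRF4 and myostatin mRNA expression levels"
- signaling markers: "GPX-3, SOD-2, Trx-1, insulin-like growth factor 1 (IGF-1), Notch1, Wnt3 protein expression levels"
- muscle redox markers: reduced and oxidized glutathione, protein carbonyls and malondialdehyde

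No marker leads, there is no composite or order of testing, and nothing says how many markers must be significant for the primary objective to be met.

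In the section on statistical analyses and power calculation, time and trial effects in the low (LR) and high (HR) respondent groups are analysed by a two-way repeated-measures "ANOVA test with a Bonferroni correction for pairwise comparisons". "The level of statistical significance will be set at" p < 0.05. The non-parametric alternative states no correction at all. The same section sizes the trial on one within-between interaction test (effect size 0.55, alpha 0.05, power 0.95, LR and HR as the two groups) and names no outcome for it.

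**The concern.** A significance level of 0.05 protects one test. Here it is applied to each of about 21 outcomes of equal rank, and a significant result on any of them could be reported as a primary finding. The Bonferroni step does not help, because it adjusts time and trial contrasts after one marker's ANOVA and never looks across markers.

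The families also answer different questions. The hypothesis in the Background concerns satellite-cell activity, yet muscle glutathione is equally primary, and the article itself describes NAC as a glutathione precursor. A shift in glutathione alone could count as a positive primary result while saying nothing about satellite cells. The Discussion expects the results to inform nutritional or pharmaceutical interventions, so a false lead has consequences.

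**Working it through.** **The plan's own figures.** The plan gives no error rate for the primary family, only the 0.05 level. Its one related figure is the sample size. The dropout step reproduces: 10/(1 − 0.15) = 11.76, hence 12 per group. The 10 per group cannot be reproduced uniquely, because the number of repeated measurements m is not stated. Reading 0.55 as Cohen's f, with noncentrality f²·N·m/(1 − 0.5), power 0.95 needs 7, 6 or 5 per group for m = 2, 3 or 4. That is a separate matter; what counts here is that the calculation covers one test at 0.05.

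**Count of primary outcomes.** Pax7+ and MyoD+ in two fiber types, 4; macrophages, 2; mRNAs, 5; proteins, 6; redox, 4. Total 4 + 2 + 5 + 6 + 4 = 21. With fiber types pooled, 2 + 2 + 5 + 6 + 4 = 19.

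**One test per marker, independent markers, no NAC effect.**

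- 21 markers: 1 − 0.95^21 = 0.659
- 19 markers: 1 − 0.95^19 = 0.623

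**Correlated markers.** The documents give no inter-marker correlation, so a common value ρ is assumed. For two-sided normal tests with c = 1.96, the chance of at least one rejection among 21 is

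x = 1 − ∫ φ(u) [Φ((c − √ρ·u)/√(1 − ρ)) − Φ((−c − √ρ·u)/√(1 − ρ))]^21 du.

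**LR and HR analysed separately.** The groups are different people, so the two sets of tests are independent and the chance is 1 − (1 − x)². With independent markers this is 1 − 0.95^42 = 0.884.

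| Assumed ρ | 21 markers, one test each | 21 markers, LR and HR separately | 19 markers, one test each | 19 markers, LR and HR separately |
|---|---|---|---|---|
| 0 | 65.9% | 88.4% | 62.3% | 85.8% |
| 0.3 | 55.5% | 80.2% | 52.5% | 77.5% |
| 0.5 | 42.9% | 67.4% | 40.9% | 65.0% |
| 0.7 | 29.5% | 50.3% | 28.3% | 48.7% |
| 0.9 | 15.7% | 29.0% | 15.3% | 28.3% |

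The expected number of false positives does not depend on ρ: 21 × 0.05 = 1.05, or 42 × 0.05 = 2.1 with separate groups.

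**Cross-check.** A simulation of the trial-by-time interaction (10 per group, two trials, three times, 21 markers, both groups, 4,000 runs) gave 88%, 81%, 70% and 54% at ρ = 0, 0.3, 0.5 and 0.7. If either a trial main effect or an interaction counts as positive, it gave 99%, 97%, 92% and 79%, so the table is not an upper limit.

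**The case against.** Four points can be made for the plan.

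1. **Separate groups.** A reader might infer that the plan fixes 42 tests and so an 88% error rate. The text does not settle this. The analysis paragraph speaks of comparisons in the two groups, which can mean separate ANOVAs, but the power calculation treats LR/HR as a between-subject factor in one model. Under that reading there is one model per marker and the 42-test count does not follow. This objection stands, so both columns are shown.

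2. **Correlation.** A reader might also infer that a false positive is more likely than not. With one test per marker that fails at ρ = 0.5 and above. Some markers are plainly linked: activated cells are identified by Pax7 and MyoD together, and M2 macrophages by CD11b and CD206 together. This stands as a limit on the size, not on the direction.

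3. **Mechanistic trial with safeguards.** The list is prespecified, effect sizes with 95% confidence intervals are promised for all dependent variables, and the primary and secondary data are to be published. These limit selective reporting but do not control type I error. It is also true that counting any one significant marker as a positive result is an assumption, since the plan has no success rule. That absence is part of the problem.

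4. **A statistical analysis plan could add a hierarchy.** It could. But this document itself fixes the primary list and the 0.05 level, and nothing in it points to a further rule.

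**Conclusion.** The point holds for the lack of error control across the primary outcomes. With 21 co-equal primaries and 0.05 applied to each, the chance of at least one false-positive primary marker is about 30% to 66% with one test per marker, and about 50% to 88% if LR and HR are tested separately. Both ranges assume no NAC effect, a common inter-marker correlation between 0 and 0.7, one p-value per marker (per group in the second range), and a positive result meaning any one significant marker. Even at a correlation of 0.9 the figures are 15.7% and 29.0%.

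The documents do not support a single headline figure, nor the inference that a pooled Pax7+ count is the only proper primary. The hypothesis concerns satellite-cell activity, not content alone, and the abstract also asks whether regeneration depends on basal satellite-cell content.

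**What to change.** Before the trial starts, choose one of two routes.

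- **One primary.** Name one marker and one test (NAC versus placebo, trial by time) that match the satellite-cell hypothesis, for example Pax7+ or Pax7+/MyoD+ cells, with the fiber type stated. Make the other families secondary, with Holm or Benjamini-Hochberg control.
- **Several primaries.** Keep them under Holm or a fixed sequence that covers every primary marker and any separate LR and HR tests. For scale, the smallest Holm threshold is 0.05/21 = 0.0024 for 21 tests and 0.05/42 = 0.0012 for 42.

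Under either route, say whether LR/HR is a factor in one model or defines separate analyses. Keep the NAC-by-LR/HR comparison as a prespecified key secondary test, so that the question on basal satellite-cell content is still answered.

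The cost is modest: no assay, visit or biopsy changes. The other markers can no longer be claimed as stand-alone primary results. The registered primary outcomes must be formally amended, and soon: the article says the trial has not commenced but recruitment is under way. The sample-size statement (effect size 0.55, one test at 0.05, no outcome named) must be tied to the chosen marker, test and alpha, and power restated if needed.

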### Participants recruitment and screening

We will initially recruit 40–60 young men. In organized meetings, participants will be informed by the investigators about the purpose of the study, the experimental procedures and all the possible risks and benefits associated. Participants will be recruited via media advertisements and posters. All volunteers will complete a health history questionnaire and a written consent form will be acquired from each participant by the investigators. All personal information and data obtained will be confidential and only the researchers of the study will have access to the database. Participants will be included in the study if they (1) are healthy, non-smokers, aged 18–30 years; (2) have a BMI of 18.5–24.9 kg/m^2^; (3) abstain from any vigorous PA during and ≥ 4 weeks prior to the study; (4) have no recent history of musculoskeletal injury, lower limb trauma and metabolic diseases; and (5) they refrain from consumption of alcohol, caffeine, any type of nutritional supplements, non-steroidal anti-inflammatory drugs (NSAIDs) and medication before (≥ 6 months) and throughout the experimental period.

### Exclusion criteria

Allergies or intolerance to NACRecent febrile illnessUse of anti-inflammatory medicationUse of medication interacting with muscle metabolism

### Exercise protocol

Participants will perform a protocol consisting of 300 eccentric unilateral maximal contractions (20 sets, 15 repetitions/set, 30-s rest between sets) of the quadriceps muscles on an isokinetic dynamometer (Cybex 770, USA) at a speed of 30°/s. A different limb will be used in each trial. Before the protocol a standard warm up will precede involving 8-min cycling on a cycle ergometer (Monark 834, 154 ERGOMED C, Sundbyberg, Sweden) at a speed of 70 rpm/min and at 50 W, followed by 5-min stretching exercises. KE will be isolated using straps in the shoulders, hips and thigh. This protocol has been described in the literature to effectively induce a significant level of skeletal muscle damage and myofibrillar disruption as documented with electron microscopy and immunohistochemistry [30, 31].

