## Methods/design

### Study overview and design

The methods and ethics of the present study have been approved by the Institutional Review Board of the University of Thessaly (ref. number 1387) and procedures are in accordance with the Declaration of Helsinki, as revised in 2013. The SpEED study incorporates a randomized, two-trial (NAC vs placebo), cross-over, double-blind, repeated-measures design. Participants who will fulfill the inclusion criteria will have their body mass, height, resting metabolic rate (RMR), body composition, muscle strength, soreness and maximal oxygen consumption (VO_2max_) measured. Since protein and antioxidant consumption as well as systematic physical activity (PA) and/or exercise may affect SCs responses and/or redox status, participants’ daily nutrient intake (via a 7-day diet recall with emphasis on protein and antioxidant intake) and PA levels (via accelerometry instrumentation) will be monitored for a week before the inception of the study [24–26]. Then, a 2-week adaptation period (only before the first trial) will be applied to adjust (through a balanced diet, using RMR values and daily energy expenditure measurements) protein and antioxidant intake at the levels required by current Recommended Dietary Allowances (RDAs) (0.8–1 g of protein/kg/day; 900 mg/day of vitamin A; 90 mg/day of vitamin C; 600 IU/day of vitamin D; 15 mg/day of vitamin E; 11 mg/day of zinc; 400 mg/day of magnesium and 55 mg/day of selenium) [27, 28]. This dietary protocol will be designed and implemented by a registered dietician. During the same time-frame, familiarization with experimental procedures will be provided.

Evidence exists that skeletal muscle growth and myogenic potential is directly related to its basal SCs content [24, 29]. As such, volunteers will provide a resting (they will abstain from any exercise or intense PA for at least 5 days prior to sampling) muscle biopsy sample (baseline sampling) from their vastus lateralis muscle (of their dominant limb) and based on its SCs content will be stratified to either high (HR) or low (LR) respondents. Participants will be stratified as HR or LR using a K-means cluster analysis. Blood sampling and performance measurements will also be performed at baseline.

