Following stratification to the HR and LR groups, volunteers of each group will then perform two trials in a randomized order: (1) NAC ingestion and (2) placebo ingestion. NAC or placebo will be consumed before (a 7-day loading phase) and after (immediately post exercise and for eight consecutive days thereafter) an intense eccentric exercise protocol. During both trials, participants will follow the balanced daily dietary protocol of the adaptation period. However, daily dietary intake will be recorded and analyzed during each trial in an attempt to minimize deviations from the prescribed diet. A 4-week washout period will be implemented between trials (dietary intake during this period will also be adjusted according to that applied during the adaptive period). During the entire experimental period, participants will be asked to abstain from any strenuous PA or exercise. Muscle biopsies and blood samples will be collected after overnight fasting before the exercise protocol (pre-exercise sampling) as well as at 2 and 8 days post exercise. Muscle strength and delayed onset of muscle soreness (DOMS) will be evaluated at the same time points. All measurements and collection of biological samples will be performed at the same time of day, in both trials, to prevent circadian rhythm variations. Figure 1 shows the Consolidated Standards of Reporting Trials (CONSORT) diagram of the study and Fig. 2 illustrates the experimental flowchart for the clinical trials.

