### Supplementation protocol

Participants will consume either NAC or placebo in a random order according to a double-blind, crossover design. A dosage of 40 mg NAC/kg/day will be administered orally in three doses (equally distributed), in order to maximize cysteine levels (for glutathione synthesis) in the circulation and skeletal muscle, primarily due to NAC fast rate of clearance (~ 6 h post ingestion) [32]. According to a model proposed by Reid in 2001, there is an optimal intracellular redox status required for optimum muscle function and force production [33]. Hence, when NAC is supplemented orally as an exogenous antioxidant (glutathione precursor), under conditions of increased oxidative stress and ROS production, it is plausible to administer a moderate dose for optimal scavenging of ROS, which according to recent studies, represents an absolute dose of ~ 1.2 to 5 g/day and evokes a pronounced improvement in muscle function and performance [34–37]. Larger doses of NAC supplementation may buffer physiological levels of cellular oxidants and may result in impaired muscle force production and performance deterioration [38]. With our dose of 40 mg/kg/day we will reach an absolute dose of approximately ~ 2.8 g of NAC for an average participant weighted ~ 70 kg. Additionally, this dosage has been shown to successfully increase total thiol levels in plasma [39]. NAC in a powder form will be diluted in a 250-ml drink containing 248 ml water and 2 ml of natural, non-caloric, flavoring-sweetener containing sucralose (Flavdrops, My Protein, Cheshire, UK). The placebo supplement will be prepared to be identical to NAC in terms of taste and smell apart from the NAC content. In both trials, each participant will be asked 15 times (once a day) if they realize whether the drink they consumed was the placebo or the experimental one. Responses will be recorded, and correct or incorrect answers will be measured. A research assistant will perform the randomization and assign participants to the interventions (NAC vs placebo) during the clinical trials using an online, computer-based, third-party, semi-automatic randomization system. The same research assistant will have full access to this list and will monitor the presence of any adverse side effects in both trials via questionnaires [30]. Both investigators and participants will be blinded to supplementation condition. Possible adverse reactions to oral NAC supplementation include an upset stomach, nausea, stomach and/or intestinal gas, sleepiness, metallic taste, light-headedness, redness of eye, face, or hands, and cough [39].

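### The treatment model for this two-period, two-limb crossover has no period, sequence or limb term, which costs power if such effects exist and biases the NAC estimate if the order is also unbalanced

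*Protocol article*

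**What the plan says.** Study overview and design describes the trial so: "The SpEED study incorporates a randomized, two-trial (NAC vs placebo), cross-over, double-blind, repeated-measures design". After stratification into high and low respondents, "volunteers of each group will then perform two trials in a randomized order", with "A 4-week washout period will be implemented between trials". Exercise protocol adds "A different limb will be used in each trial", each bout being 300 maximal eccentric contractions. Supplementation protocol says that interventions are assigned "using an online, computer-based, third-party, semi-automatic randomization system"; limb is not mentioned there.

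Statistical analyses and Power calculation states that time and trial effects in the two respondent groups "will be analyzed using a two-way repeated-measures ANOVA test with a Bonferroni correction for pairwise comparisons". The factors are time and trial (NAC or placebo). The non-parametric fallback (Friedman, Wilcoxon, Kruskal-Wallis, Mann-Whitney) has no period, sequence or limb term either. At least 12 men per respondent group are to be selected.

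**The concern.** In a crossover, each man's NAC-minus-placebo difference contains the treatment effect plus or minus any difference between his two periods. Here it also contains any difference between his two limbs. A model without these terms treats that systematic variation as noise if the orders are balanced, and attributes part of it to NAC if they are not.

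The article gives reasons not to take periods and limbs as interchangeable:

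- The men do the second bout after having done the first, on the other leg.
- As Study overview and design describes it, the baseline biopsy comes from the dominant limb, so that limb is sampled four times and the other three.
- mRNA results are expressed as fold changes from baseline. If the only baseline is from the dominant limb, the other limb's trial is referenced to a different limb, and even a constant limb difference remains in those changes.
- Strength and soreness are measured on the exercised limb, so they change limb between trials.
- Dietary adaptation is unequal: "a 2-week adaptation period (only before the first trial) will be applied". This one is largely offset (see the objection).

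At stake are the power of the NAC comparison in groups of about 12 and, if the order comes out uneven, the estimate itself.

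**Working it through.** **Inputs.** The group size is the article's: 10/(1 − 0.15) = 11.8, so 12 per group; this step reproduces. The 10 that enters it does not follow from the stated inputs. The number of measurements is not given; trying 2, 3, 4, 5, 6 and 8 gives a total, not per-group, requirement of 14, 12, 10, 8, 8 and 6. That calculation contains no period or limb input, and the present point does not rest on it. The size of any period or limb effect is not in the document, so it is an **assumption**: π = 0.25, 0.5 or 1.0 SD of the within-person difference.

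**Model.** For man *i*, d_i = τ + s_i·π + e_i. Here τ is the NAC effect, s_i = ±1 is the order (or the limb used with NAC), and e_i has SD 1. The unadjusted analysis is a one-sample t-test on d; the adjusted one adds s as a factor.

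**Balanced order (6:6).** The expected variance used by the unadjusted test is 1 + π²·n/(n − 1) = 1 + 1.091π². The SE ratio, unadjusted to adjusted, is its square root:

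| π (SD) | SE ratio | Power unadjusted (80% adjusted) | Size unadjusted |
|---|---|---|---|
| 0.25 | √1.068 = 1.03 | 79% | 4.4% |
| 0.5 | √1.273 = 1.13 | 73% | 3.0% |
| 1.0 | √2.091 = 1.45 | 49% | about 0.6% |

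The τ that gives 80% power when adjusted is 0.90 SD. Power and size were simulated.

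**Unbalanced order.** Bias = π(n₁ − n₂)/n. At 8:4 this is π × 4/12 = π/3, or 0.08, 0.17 and 0.33 SD. At 9:3 it is π/2. At 8:4 the unadjusted size stays near 5%, because the larger SE offsets the bias; the estimate is still wrong. At 9:3 the size is 6.0%, 9.2% and 15.0%. With the order as a factor, bias is about 0 and size about 5% in both cases. If randomization were simple (the article does not say), 12 men would split 6:6 with probability 0.23 and 8:4 or worse with probability 0.39.

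**Which contrast is affected.** Take three times (pre-exercise, day 2, day 8), with the NAC-minus-placebo differences correlated 0.5 between times (assumed), 12 men, balanced order. The variance of the mean over times is (1 + 2 × 0.5)/3 = 0.667; that of the change from pre-exercise is 1 + 1 − 2 × 0.5 = 1.

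- Effect constant over time: the trial main effect has SE ratio √(1 + 1.091π²/0.667) = 1.19 at π = 0.5 and 1.62 at π = 1. The change from pre-exercise has ratio 1.00, because the effect cancels.
- Effect on post-exercise values only: the change has ratios 1.13 and 1.45, and the trial main effect 1.09 and 1.31.

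**Price of adjusting when π = 0.** At τ = 0.90 SD, power is 80.8% with 11 error degrees of freedom, 80.0% with 10 and 79.0% with 9: about one point per term.

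**The case against.** The strongest reply has five parts.

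- *Limb order and blocking are matters of silence.* This stands. A reader might infer that limb order is not randomized and that sequences are not balanced within respondent groups. The article says neither. It says only that the limb changes and the treatment order is random, and an article commonly leaves block sizes and limb allocation to the full protocol. The 39% figure is likewise conditional on simple randomization.
- *Known differences are mitigated.* Partly stands. The washout diet follows the adaptation diet, so the second trial is also preceded by controlled intake. Biopsies are spaced 5 cm apart to limit a repeated-biopsy effect, and the abstract lists baseline among the sampling times in both trials, so the extra dominant-limb biopsy is not settled. Using the other limb is itself a safeguard, and the document gives no evidence that one leg's bout alters the other's response. None of this shows that period and limb effects are absent.
- *The magnitude is assumed.* Stands. At 0.25 SD the loss is one power point.
- *A constant effect cancels in trial by time.* Stands for changes from the same limb's pre-exercise value. It does not protect the trial main effect, nor any contrast if the second bout produces a different response.
- *Random order gives no bias on average.* True: averaged over random orders, bias is zero and size about 5%. But one split will be obtained, and the bias given that split is what the report will carry.

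**Conclusion.** The point holds as a weakness in a stated analysis choice: the named ANOVA omits period, sequence and limb from a two-period crossover with a limb switch. Both consequences are conditional. Loss of power needs a non-zero period or limb effect. Over an assumed 0.25 to 1.0 SD, with balanced order and 12 men, it ranges from negligible (79% against 80%) to serious (49%), and the test errs towards caution. Bias needs such an effect and an unbalanced split, and equals their product. A reader might conclude that the planned analysis is biased as it stands, or that standard errors will certainly be inflated; the document supports neither. Since adjustment is cheap and the article reports that the trial has not commenced, the change should be made, but the design is not invalid without it.

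**What to change.** Replace the two-way ANOVA by a model with trial, time, trial by time, period and period by time. Add limb and limb by time unless limb is aliased with period (for example, if every man starts on the same limb, one set of terms covers both). Keep random effects for participant and for participant-by-trial.

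Both details matter:

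- Period as a main effect only is not enough. In simulation with an 8:4 split and a period effect of 0.5 or 1.0 residual SD on post-exercise values, the NAC change remained biased by 0.17 and 0.33, the full one third.
- A participant effect alone is not enough. With participant-by-trial variance of 0.25, 0.5 and 1 times residual (assumed), simulated size for the trial effect was roughly 11–12%, 15–16% and 21–22%.

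An equivalent, simpler route with complete data is to take each man's NAC-minus-placebo difference in change from pre-exercise and analyse it with sequence as a factor (and limb where needed), estimating the NAC effect as the unweighted mean of the sequence means.

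State how treatment sequence and first limb are allocated. If the full protocol does not already balance them, do so jointly within high and low respondents: four combinations, three men each at 12 per group.

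The cost is analysis wording, possibly a setting in the randomization system, and a few error degrees of freedom: about one power point per added term if there is no such effect.
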